### Procedures

#### Study 1

Recruitment: A nationwide promotion will be launched across all MLs in France through the National Union of Local Missions (Union Nationale des Missions Locales: UNML) and the Regional Association of Local Missions (Association Régionale des Missions Locales: ARML). A flyer is designed to be sent out or displayed within the MLs. Each ML involved will send emails to registered young people. It includes detailed information about the research, a link to access the study and inclusion criteria (see: Table 1). Upon accessing the study’s homepage, participants will find an introductory note presenting the study, its objectives, a contact point for further information, and a link to open the questionnaire. This will lead to a consent form. To the question, “Do you consent to participate in this research?” participants will be able to answer “Yes” or “No.” Participants who select “Yes” access the questionnaire. Those who select “No” will not be able to continue.

#### Study 2

Recruitment: The qualitative study is addressed to psychologists currently working at the ML and having at least one young adult in their active caseload. A communication will be made by the UNML and ARML. After a presentation of the study by the researcher, the psychologists will receive an information sheet (see: supplementary material) detailing the study’s objectives, methodology, duration, constraints, and risks. The volunteer psychologists will then have 15 days to reflect and formalize their consent (see: supplementary material) by signing the dedicated form.Interview: After this period, each participant will be interviewed for a one-hour semi-structured session. The study can be conducted in person, via videoconference, or by telephone, according to the participant’s preference, but always under conditions that respect privacy. All interviews will be recorded using a voice recorder and will not collect any identifying data. The interviews will be transcribed, and the audio recordings destroyed after the topics have been validated by inter-rater agreement (according to the CQR method). Confidentiality will thus be guaranteed.

#### Study 3

Recruitment: The longitudinal study is intended for young people from MLP. Young people will be recruited through an explanatory email and the distribution of a flyer in the 6 MLP. Young people who have expressed interest will be interviewed by a member of the research team to verify their eligibility (see: Table 1), provide them with a detailed information sheet (see: supplementary material), and answer any questions. Eligible persons will then have 15 days to consider their decision and formalize their participation by signing the informed consent form (see: supplementary material).Randomization procedure: Participants will be assigned to one of two arms using a single-blind randomization procedure (1:1 allocation ratio). The assignment will be handled by a researcher who will not perform the data analysis, using a computer and a random number generator. The sequence will be stored in a secure file until participant enrollment is completed. Due to the nature of the intervention, neither the participants nor the facilitators (partner psychologists) can be blinded to group membership. However, the analysts of the outcome data will remain blinded to this group membership during statistical analyses. No formal unblinding procedure is planned, as there is no blinding at the participant level.Intervention and comparator: The control group will receive food assistance once a week for 12 months. The experimental group will receive the same food aid and in addition, psychological support twice a month for 6 months. The psychological support consists of individual sessions conducted by experienced psychodynamic psychologists and partners of the MLP. Food aid consists of distributing food baskets from MLP partner associations. The services are already offered by the MLP and are simply being reorganized within the framework of the study. In order not to deprive participants of potential care, the comparison of these two distinct approaches was guided by strong ethical considerations.Assessments and outcomes: These conditions enable the effects of different types of interventions to be measured within a supportive framework. Each participant will have 4 evaluation times during the year (T0, T1, T2, T3). Each time, they will first complete standardized scales and then have a semi-structured interview (see: Fig. 1). The interview will aim to characterize the participant’s experience, gather information about their history (T0), and assess their adherence to the proposed follow-up care, living conditions, interpersonal relationships, and future projections (T1, T2, T3). A closing session (T3) will also allow for a retrospective evaluation of the experience of the program, the maintenance of its effects, and the desire to continue the follow-up care. The primary outcome is the change in food insecurity level between baseline (T0) to 12 months (T3). Secondary outcomes include: (1) change in depressive symptoms (PHQ-9 score), change in anxiety symptoms (GAD-7 score), change in PTSD and CPTSD symptom dimensions (ITQ criteria) and change in defensive functioning (DSQ-40 scores). Adherence to food assistance and/or psychological support and any change in participant situation will be documented based on self-report during semi-structured interviews.

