## Method/design

This research project is designed around three distinct methodological approaches. These phases are complementary (see: Table 1).

A cross-sectional study (study 1) based on a quantitative approach, consisting of the widespread distribution of standardized online questionnaires and scales (see: Measures) to young adults receiving support from any ML nationwide.The instruments facilitate a systematic collection of quantitative data and a multidimensional analytical framework to model the associations between psychological and social vulnerability factors. This design supports the identification of overarching statistical patterns.A qualitative study (study 2) intended for psychologists within MLs. This exploratory study offers a complementary perspective on understanding the experiences of youth at the MLs. By collecting data through verbatim analysis this study helps to identify some of the individual and institutional issues that influence the dynamics of care in these structures.An interventional longitudinal study (study 3) comparing two support programs. It is a multicenter, two-arm, parallel-group, single-blind randomized controlled trial. Participation is voluntary for young people experiencing severe FI and psychological distress, with a history of ACE, exclusively from MLP. The control group receives weekly food assistance for 12 months. The experimental group benefits from an intervention combining weekly food assistance for 12 months and twice-monthly psychological follow-up for 6 months. The study follows a superiority framework, hypothesizing that the combined intervention (food assistance plus psychological support) will lead to greater improvements in psychological distress and FI level compared to food assistance alone.

*Participants are assessed 4 times (T0: start of the program*,* T1: 3 months after the beginning*,* T2: end of the psychological intervention (6 months after the beginning)*,* T3: end of the program (12 months after the beginning). Each assessment period allows for the measurement of changes over time through standardized scales and semi-structured qualitative interviews. Detailed analyses will enable comparison of the specific effects of each intervention.*

**Table 1 Tab1:** Summary table of the research methodology

	Study 1	Study 2	Study 3

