Type of study Method	Quantitative Cross-sectional study using self-administered questionnaires	Qualitative Semi-structured interviews	Longitudinal Intervention programs Self-administered questionnaires and semi-structured interviews
Eligibility criteria	Participant aged 18–25 Currently being supported by the Mission Locale	Being a psychologist Currently working at the Mission Locale Have at least one young adult in their active caseload	Participant aged 18–25 Currently enrolled in an insertion program in the Mission Locale Answer “yes” at item 8 of the FIES PHQ-9 score > 15 GAD-7 score > 10 exposed to one or more ACEs (CTQ-SF)
Exclusion criteria	Minors Do not speak and read French Under Guardianship or Curatorship Unable to provide informed consent	Not having psychological follow-up at the Mission Locale Unable to provide informed consent	Minors Do not speak and read French Under Guardianship or Curatorship Unable to provide informed consent Currently receiving psychiatric care for an acute or chronic mental illness requiring regular specialized treatment Presenting a social or medical emergency situation incompatible with the study Having already participated in a similar study or being currently engaged in a structured psychological intervention protocol
Main Outcomes	Food Insecurity prevalence Mental health aspects (anxiety, depression, PTSD and CPTSD) Childhood trauma Psychological resources (defense mechanisms, resilience, perceived social support) Substances use Quality of sleep	Psychological practice and working conditions Organization of care Perspective on the young people encountered Sensitivity to issues of trauma and vulnerability	Childhood trauma Mental health aspects (anxiety, depression, PTSD and CPTSD) Food Insecurity level Defense mechanisms Anamnesis, current living conditions, adherence and perception of interventions
Analysis	Quantitative analysis	Thematic analysis	Quantitative and qualitative analysis

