##### Food Insecurity Experience Scale (FIES) [32–34]

An 8-item measure assessing the severity of food insecurity experienced, based on difficulties accessing adequate food.

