### Data monitoring and management

As data monitoring responsibilities are shared among the research team members, no data monitoring committee has been appointed. Data entry will be verified twice to ensure accuracy, and data quality will be assured through range checks. Participants will receive reminders. If they do not attend the appointments (study 3), reminders will be sent by text message or email. Data already collected from participants who have ended their participation will be retained for analysis. All data will be pseudonymized via a lookup table during the active phase of the study. After this, the lookup table will be destroyed to render the data completely anonymous. Considering the minimal-risk nature of the study, it will only be discontinued prematurely in case of unforeseen ethical concerns.

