### Safety considerations

The instruments used in this study are standardized and validated questionnaires. They have been widely used in previous studies involving young and vulnerable populations, often through self-administration. Their use does not present any specific identified risks, apart from possible occasional discomfort when reflecting on certain personal situations.

Regarding the qualitative interviews in Study 2, no adverse effects are expected. However, the semi-structured interviews in Study 3 comprise a period for gathering information and subjective experiences, particularly during the initial meeting. Although conducted in a respectful and non-intrusive manner, these exchanges may potentially elicit emotions related to past or present events, especially in the context of a history of precarious living conditions, family instability, or childhood adversity.

To mitigate this risk, all interviews will be conducted by experienced psychologists trained in trauma clinical practice and in gathering information in vulnerable situations. In cases of obvious distress or a perceived need for more specific support, participants can be immediately referred to the psychologists at the ML.

If a psychiatric evaluation is deemed necessary a referral to a partner psychiatrist can be made. These resources are available regardless of the participant’s assigned group.

All of these measures help minimize potential psychological risks and ensure rapid and appropriate support when needed. If an exclusion criterion is met during the study, participation will be stopped.

Withdrawal of participants is entirely voluntary and will have no consequences, thus ensuring adherence to ethical research principles. Withdrawal of consent during data collection constitutes termination of participation. Participants who cease participating in research interviews or discontinue their participation in the support program will be considered lost to follow-up.

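### The loss-to-follow-up rule ties outcome collection to continued interviews and programme attendance, although every outcome scale is self-administered and could still be sought

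*Protocol article*

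**What the plan says.** Study 3 assesses participants at T0, T1, T2 and T3. Procedures (Study 3, assessments and outcomes) sets the order at each visit: "Each time, they will first complete standardized scales and then have a semi-structured interview". The primary outcome is the change in food insecurity level from T0 to T3. Measures lists the FIES for this, described as "An 8-item measure assessing the severity of food insecurity experienced, based on difficulties accessing adequate food". The secondary outcomes come from the PHQ-9, GAD-7, ITQ and DSQ-40. Table 1 names two methods for Study 3: "Self-administered questionnaires and semi-structured interviews". The interview's stated aims are experience, history, adherence, living conditions, relationships and plans.

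Two further passages decide what happens when someone stops coming. Data monitoring and management says: "If they do not attend the appointments (study 3), reminders will be sent by text message or email". It adds that data already collected from people who have ended participation are kept. Safety considerations says: "Participants who cease participating in research interviews or discontinue their participation in the support program will be considered lost to follow-up".

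Study 1 is delivered as "standardized online questionnaires and scales". Its battery includes all five of the Study 3 outcome scales.

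**The concern.** The rule under Safety considerations joins two conditions with an or. A person still collecting food baskets who stops only the interviews is classed as lost. So is a person who leaves the support programme but would still answer a questionnaire. Neither event stops anyone from completing a self-administered scale. Only withdrawal of consent or failure to return the scale does that.

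Two things are at stake.

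- **Precision.** Study 3 plans 35 people per arm with no power calculation, so each avoidable missing 12-month value counts.
- **Bias.** Participants are selected for high PHQ-9 and GAD-7 scores and exposure to childhood adversity, and the protocol itself expects that the interviews may stir emotions tied to that history. It is plausible, though the document does not say so, that people stop attending when they feel worse. Leaving the programme may also be related to outcome, and counting leavers as lost weakens a comparison by randomized group.

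**Working it through.** **Step 1. Does the outcome need the interview?**

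| Item | Where | Content |
|---|---|---|
| Primary outcome | Procedures, Study 3 | Change in food insecurity, T0 to T3 |
| Instrument | Measures, Study 3 | FIES, 8 items |
| Secondary scales | Procedures and Measures | PHQ-9 (9 items), GAD-7 (7), ITQ (18), DSQ-40 (40) |
| Mode | Table 1 | Self-administered, listed apart from the interviews |
| Interview aims | Procedures, Study 3 | No primary or secondary outcome scale among them |

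It does not. The five scales total 8 + 9 + 7 + 18 + 40 = 82 items. The FIES, PHQ-9 and GAD-7 are short; the full set is not.

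**Step 2. Who would lose the 12-month value under the rule?**

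- Attends T3, completes the scales, declines the interview: the scales come first and collected data are kept, so the primary outcome is in hand.
- Misses one appointment: a reminder is sent. The rule speaks of ceasing interviews, not of missing one.
- Stops interviews, or leaves the programme, before T3: classed as lost. Earlier values are kept, but no later collection is described.

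Only the third group is affected.

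**Step 3. Size.** Study 3 states no power, effect size, standard deviation or dropout rate, so there is no figure of the plan's own to reproduce. The following is an illustration.

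Inputs: 70 participants (Participants, Study 3). Assumed: a share L missing at T3, of which half would return an online form.

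- Available without recovery: 70 × (1 − L). For L = 20%: 70 × 0.80 = 56. For L = 35%: 70 × 0.65 = 45.5.
- Available with half recovered: 70 × (1 − L/2). For L = 20%: 70 × 0.90 = 63. For L = 35%: 70 × 0.825 = 57.75.
- Ratio of standard errors of the arm difference, complete cases, equal arms: the square root of (available without ÷ available with). √(56/63) = 0.943 and √(45.5/57.75) = 0.888.

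The standard error falls by about 6% to 11%.

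The same comparison as power (normal approximation, two-sided α = 0.05, 1:1, complete cases): with 35 per arm, a standardized difference of 0.67 is detectable with 80% power.

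| Assumed loss at T3 | Per arm | Power for 0.67 | Per arm, half recovered | Power for 0.67 |
|---|---|---|---|---|
| 20% | 28 | 71% | 31.5 | 76% |
| 30% | 24.5 | 65% | 29.75 | 73% |
| 40% | 21 | 58% | 28 | 71% |

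**The case against.** A reader might infer that the scales are collected only at the interview appointment, and that anyone who declines an interview yields no outcome data. The document supports neither. Procedures fixes an order, not a place, and excludes no other route. The study flowchart is not reproduced in the text available, and a condensed article may leave the mode of completion to the full protocol. Someone who attends and then declines the interview has already given the FIES. T0 and every completed visit are kept.

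The analysis also softens the loss. The planned mixed model uses repeated scores, so missingness explained by earlier values of the same outcome can be accommodated, and multiple imputation may be considered above 5% missing. The document does not say that distress causes non-attendance, or does so more in one arm. The 6% to 11% rests on two assumed rates. It applies recovery to all non-attenders and ignores what T1 and T2 contribute to the model.

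All of that stands, and it limits the size and reach of the point. What remains is the rule itself. It is an express definition, not a detail left out for space, and it equates stopping interviews or the programme with loss to follow-up. A remote route in the full protocol would not correct that definition. The mixed model and standard imputation also do not remove bias when missingness depends on current distress that was never measured. Collecting the scale addresses that directly.

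**Conclusion.** The point holds as a cheap improvement, anchored on the loss-to-follow-up sentence in Safety considerations. As written, the rule ties outcome follow-up to interviews and to staying in the programme, although the outcome scales require neither. With reminders the only described response to non-attendance, obtainable values at T1 to T3, including the primary outcome, are not described as being sought from people who stop before T3.

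The size cannot be derived from the documents, because they give no attrition rate and no indication of how many non-attenders would still answer a questionnaire. With 20% to 35% missing at T3 and half recovered, the complete-case standard error falls by about 6% to 11%. The gain under the mixed model may differ. Less bias from distress-related missingness is a plausible benefit, not a demonstrated one.

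**What to change.** In Safety considerations, distinguish three events: stopping the research interviews, stopping the support programme, and withdrawing consent to outcome collection. State that, unless consent is withdrawn, the scales are still sought at T1, T2 and T3 after either of the first two.

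In Data monitoring and management, add to the reminders already planned a link to an online version of the FIES, PHQ-9, GAD-7, ITQ and DSQ-40. Adapt it from the Study 1 forms, place the FIES first because the set runs to 82 items, and tie it to the participant's pseudonymized identifier. Count a participant as lost for an outcome only when that scale is not returned. Record the mode of completion and report it by arm.

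The cost is some set-up work, since the article describes no participant identifier for the Study 1 forms and Study 3 returns must be linked to one. Some participants will have mixed modes of completion, possibly unevenly between arms, which is why mode should be reported by arm. The support offered to either arm does not change.

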
**Fig. 1 Fig1:**
[figure not shown]
Procedure flowchart for longitudinal study (study 3). This diagram outlines participant enrolment, allocation to intervention arms, assessment time points, and follow-up over the 12-month study period

### Measures

#### Study 1

The questionnaire consists of a sociodemographic section follows by standardized scales. In order of presentation, the questionnaires are:

##### Childhood Trauma Questionnaire Short Form (CTQ-SF) [30, 31]

A 28-item instrument evaluating various types of childhood trauma, including emotional, physical and sexual abuse, and emotional and physical neglect. An additional item has been included in this scale assessing commercial child sexual exploitation.

##### Food Insecurity Experience Scale (FIES) [32–34]

An 8-item measure assessing the severity of food insecurity experienced, based on difficulties accessing adequate food.

##### Patient Health Questionnaire-9 (PHQ-9) [35, 36]

A 9-item tool used for depression screening that also provides an indication of the severity of depressive symptoms.

##### Generalized Anxiety Disorder (GAD-7) [37–39]

A 7-item self-report questionnaire designed to assess the patient’s anxiety levels over the previous two weeks.

##### International Trauma Questionnaire (ITQ) [40, 41]

An 18-item self-report measure of PTSD and CPTSD symptoms based on ICD-11 criteria. It includes clusters of PTSD, clusters of DSO and functional impairment for both clusters.

##### Insomnia Severity Index (ISI) [42, 43]

Sleep difficulties will be assessed using the first three items of the ISI (Item 1: a, b, c), which specifically address nighttime complaints: difficulty falling asleep, difficulty maintaining sleep, and early awakenings. Each item is rated on a five-point Likert scale ranging from 0 ("no problem") to 4 ("very severe problem"). The total score, obtained by summing the item scores, ranges from 0 to 12, with higher scores indicating more significant nighttime sleep difficulties.

To limit the administration workload and reduce conceptual overlap with other instruments in the protocol, only these three items were included. The dimensions relating to daytime impact, sleep-related distress and overall dissatisfaction, also assessed in the full version of the ISI, are in fact already partially taken into account by the Patient Health Questionnaire-9 (PHQ-9) and the Generalized Anxiety Disorder-7 (GAD-7), which respectively assess depressive symptoms, anxiety and impairments in functioning.

##### Alcohol Use Disorders Identification Test (AUDIT) [44, 45]

A 10-item questionnaire designed to identify individuals at risk of alcohol addiction, addressing alcohol consumption, dependence, and related problems.

